## Abstract

**Background:**

Patients with sepsis syndromes in comparison to general intensive care patients can have worse outcomes for physical function, quality of life and survival. Early intensive care rehabilitation can improve the outcome in general Intensive Care Unit (ICU) patients, however no investigations have specifically looked at patients with sepsis syndromes. The 'i-PERFORM Trial' will investigate if early targeted rehabilitation is both safe and effective in patients with sepsis syndromes admitted to ICU.

**Methods/Design:**

A single-centred blinded randomized controlled trial will be conducted in Brisbane, Australia. Participants (n = 252) will include those ≥ 18 years, mechanically ventilated for ≥ 48 hours and diagnosed with a sepsis syndrome. Participants will be randomised to an intervention arm which will undergo an early targeted rehabilitation program according to the level of arousal, strength and cardiovascular stability and a control group which will receive normal care.

The primary outcome measures will be physical function tests on discharge from ICU (The Acute Care Index of Function and The Physical Function ICU Test). Health-related quality of life will be measured using the Short Form-36 and the psychological component will be tested using The Hospital Anxiety and Depression Scale. Secondary measures will include inflammatory biomarkers; Interleukin-6, Interleukin-10 and Tumour Necrosis Factor-α, peripheral blood mitochondrial DNA content and lactate, fat free muscle mass, tissue oxygenation and microcirculatory flow.

**Discussion:**

The 'i-PERFORM Trial' will determine whether early rehabilitation for patients with sepsis is effective at improving patient outcomes with functional and physiological parameters reflecting long and short-term effects of early exercise and the safety in its application in critical illness.

**Trial Registration:**

Australia and New Zealand Clinical Trials Register (ANZCTR): ACTRN12610000808044

## Background

Critical Illness and trauma are the primary sources of intensive care unit admissions. An estimated 2-11% of these patients require prolonged stays in the ICU which accounts for 25-45% of total ICU days [1]. Survivors of intensive care, especially those with prolonged admissions, may exhibit severe psychological and physical problems [2] and have a lower health-related quality of life up to one year following discharge from the hospital [3]. Almost a quarter of these patients are either admitted with or develop sepsis i.e. a severe, specific inflammatory response to infection, during the course of their stay in the ICU with major immediate and long-term effects on morbidity and mortality [4]. Patients with sepsis can have a worse outcome both in terms of overall functioning and mortality rates [5]. There is evidence that specific decreases in muscle mass and muscle force occur in sepsis syndromes caused by a variety of mechanisms [6]. This has major effects on the health and productivity of survivors as well as ultimately impact on the availability of ICU and hospital beds, surgical waiting lists, health costs and society.

Hypothesising that light to moderate exercise can partially reverse this condition without causing harm to critically ill patients, several exercise trials conducted in general intensive care patients have indicated positive findings that early intervention with exercise is able to prevent critical illness weakness syndromes, loss of muscle mass, decrease duration of mechanical ventilation, length of hospital and ICU stay and improve overall quality of life [7]. Specifically however, it is important to investigate early rehabilitation in patients with sepsis syndromes as the inflammatory process in sepsis can aggravate and accelerate the rate of muscle wasting in addition to the immobility associated with the disease in its early stages. It is equally important to ensure that early exercise in sepsis does not result in oxidative stress or cause substantial tissue injury potentially worsening the inflammatory reaction. The physiological reasons for improvement or adverse effects require investigation (Figure 1).

**Figure 1 F1:**
[figure not shown]
**Impact of delayed ICU rehabilitation in early sepsis**. This diagram illustrates the sequential impact of delayed rehabilitation for patients with sepsis as a result of the inflammatory processes and the detrimental short and long-term outcomes.

### Sepsis Syndrome

Sepsis is a systemic inflammatory response associated with an infectious insult. It is the leading cause of death in critically ill patients and is often associated multi organ failure [8]. The inflammatory cytokines associated with sepsis such as Interleukin-6 (IL-6), Interleukin-10 (IL-10) and Interleukin-1β (IL-1β) are found to be correlated with the severity of the disease, the evolution of organ failure as measured by the SOFA score and mortality [9]. Physiological responses to inflammation as described in Table 1 in addition to the presence of a suspected or proven infection has been an internationally accepted definition for "Sepsis" [8,10]. Increasing sepsis severity correlates with increasing mortality, rising from 25-30% for severe sepsis to 40-70% for septic shock [11].

**Table 1 T1:** Criteria for SIRS and Sepsis syndromes (modified from Dellinger et al [57])

Syndrome	Criteria	Mortality
Systemic inflammatory response syndrome (SIRS) any two or more of the following criteria	▪ HR>90 bpm ▪ RR>20/min or PaCO_2_< 32 mmHg ▪ WCC< 4 × 10^9 ^cells/L or > 12 × 10^9^ cells/L or > 10% immature bands 12,000 ▪ T>38°C or <36°C	

Sepsis	▪ SIRS + proven infection	15%

Severe sepsis	▪ Sepsis + failure of one or more organs	20%

Septic shock	▪ Severe sepsis + cardiovascular failure despite adequate fluid resuscitation (usually SABP <90 mmHg or >40 mmHg from baseline)	45%

HR; Heart rate, RR; Respiratory Rate; WCC; White Cell Count; T; Temperature, SIRS; Systemic Inflammatory Response Syndrome, SABP; Systolic Arterial Blood Pressure.

### Systemic Inflammation and Proteolysis

The aggressive inflammatory process that occurs during sepsis also affects muscle force, muscle mass and ultimately physical function [12,13]. Persistent elevation of circulating levels of Interleukin-6 (IL-6) have been known to infiltrate myocytes with inflammatory factors such as prostaglandins leading to proteolysis, myocyte degeneration, and muscle atrophy [14]. Tumour Necrosis factor-α (TNF-α) overexpression in sepsis is linked to the development of cachexia [15] through endothelial dysfunction, leading to myocyte apoptosis, reduction in skeletal muscle mass, weakness and myopathy. It has been hypothesised that the prevention of excessive release of pro-inflammatory cytokines [15], and activation of proteolytic pathways leading to limitation of free-radical generation [16] may inhibit the catabolic skeletal muscle changes in sepsis [17] and thus critical illness weakness syndromes.

### Inflammatory Biomarkers and Exercise

Interleukin-10 (IL-10); an anti-inflammatory cytokine is thought to inhibit proteolysis [18] while low levels have been postulated to lead to excessive inflammation and muscle damage [19]. IL-10 is known to attenuate the synthesis of TNF-α surface receptor and its suppressive effects may be beneficial in pathology that results from inflammatory dysregulation such as in sepsis.

A number of studies [20-22] in healthy and other diseased populations; such as in chronic heart failure, have shown that aerobic and resisted exercise alters pro-inflammatory cytokines specifically decreasing IL-6 and TNF-α and increasing IL-10. Simple physical exercises such as repetitive passive muscle stretches have been shown to decrease pro-inflammatory cytokine (IL-6), increase anti-inflammatory cytokine (IL-10) and improve the IL-10/TNF-α ratio in chronic critically ill patients [23]. The use of electrical muscle stimulation on major muscle groups has been shown to attenuate the production of TNF-α [24]. It is therefore important to investigate the effect of exercise on IL-10 in sepsis.

Our pilot study tested 20 patients with sepsis syndromes randomised into a treatment (proactive rehabilitation) and a control group. The trial demonstrated significant decreases (-7.2%) in the percentage fat free mass in the control group with no decreases in the intervention group. Significant increases in IL-10 (mean difference 12.1 [SE +/- 2.1], p < 0.01) were found in the treatment group. Clinically relevant findings from this study indicate early exercise reduces loss of muscle mass in sepsis [25].

### Oxidative stress

Oxygen-derived free radicals play an important role in the development and progression of disease in critically ill patients resulting in increases in the level of Reactive Oxygen Species (ROS) [26] or decreases in antioxidant defences [27] causing oxidative stress [28]. ROS can play a pivotal role in stimulating the inflammatory system by causing an increase in cytokines (e.g. Interleukins and TNF-α). Both cytokines and ROS can enter the circulation and mediate systemic inflammatory responses linked with clinical conditions [29] which are inter-related in causing muscle proteolysis resulting in the induction of sepsis-induced myopathy [6].

In patients with sepsis, antioxidant depletion has been found to be associated with mitochondrial dysfunction where oxidative stress generates bioenergetic failure [30] which may affect changes in mitochondrial DNA (mtDNA) quantity [31], as well as increase mutations or deletions. This has been hypothesised to be part of the mechanism underlying multiple organ failure and death [32,33].

Oxidative stress also acts as an atrophic stimulus in an unloaded muscle [34] promoting wasting by modifying redox-sensitive processes in its muscle fibres such as during periods of disuse in locomotor skeletal muscles [35] and the unloaded diaphragm during prolonged mechanical ventilation [36,37]. Currently, however, there is no published data on the effects of exercise on oxidative stress on the critically ill population particularly in sepsis.

### Illness Severity

Hyperlactaemia is a marker of illness severity in sepsis [38,39]. During early sepsis, perturbation of glycolytic mechanisms can occur. In septic shock, high concentrations of circulating adrenaline can derive large quantities of lactate out of skeletal muscles, overwhelming lactate clearance mechanisms with resultant, hyperlactaemia [40,41]. The effect of light exercise on lactate clearance mechanisms in early sepsis remains to be investigated.

### Microcirculation and Muscle Oxygenation

Sepsis impairs microcirculatory function causing tissue hypoxia [42]. This, combined with blood flow diversion from less important tissues to vital organs [43] promotes decreased muscular oxygen extraction [44]. However, the use of electrical stimulation [45] on major muscle groups and a physical exercise rehabilitation program in chronic heart failure patients [46] have demonstrated short-term beneficial systemic effects on microcirculation. The effect of early activity on microcirculation in patients with sepsis should be further investigated.

### Early Rehabilitation may Modulate Detrimental Effects of Sepsis

The roles of pro-inflammatory cytokines, mitochondrial changes and muscle proteolysis in causing sepsis-induced myopathy in critically ill patients are hypothesised from animal models [6,14]. It is postulated that exercise can modulate cytokine levels [47], ROS production [50] and ATP levels [49] in patients with sepsis. In conjunction with an early mobility protocol, ambulation during mechanical ventilation in the early stages of critical illness is becoming widely practiced [50-52], especially with interruption of sedation [53-55]. Conservatively, simple passive movements [56] and neuromuscular electrical stimulation [45] as a precursor to active mobilisation can induce microcirculatory changes that may attenuate the anti-inflammatory effects in early sepsis.

Overall, early rehabilitation in critical illness seems to show reduced time on the ventilator, improved quality of life and reduced hospital and ICU stay [7] but this is not specific to sepsis. Furthermore, the short-term systemic effects of exercise for ICU patients remain highly speculative and debatable. The impact of exercise in the early stages of critical illness on effects such as oxidative stress and microcirculatory alterations have been unexplored and speculated from other populations. Exploring these physiological factors in response to exercise can contribute to determining the safety of early rehabilitation in sepsis.

### Hypotheses and Aims

The primary research hypothesis of the "i-PERFORM Trial" is that patients with defined sepsis syndromes [57] in the ICU who participate in an early targeted rehabilitation program will have improved physical function and an improved quality of life. The secondary hypotheses is that there will be systemic effects underlying primary improvements which will include; increased fat free mass; decreased pro-inflammatory and increased anti-inflammatory cytokines; increased peripheral blood mitochondrial DNA content and reduced blood lactate levels; and improved tissue oxygenation and microcirculation flow.

## Methods/Design

### Methods and Design

The i-PERFORM Trial is a prospective double blinded randomised controlled trial (RCT) in patients with sepsis syndromes randomised into an early rehabilitation intervention arm or a control arm during the course of ICU stay. All outcomes will be measured by a blinded assessor from the research team. This study is being conducted in a quaternary level general Intensive Care Unit at the Royal Brisbane and Women's Hospital (RBWH), Brisbane, Queensland, Australia. The Human Research Ethics Committee at RBWH and the Medical Research Ethics Committee at The University of Queensland have approved this study. The study protocol is registered with the Australian New Zealand Clinical Trials Registry (ANZCTR). Figure 2 illustrates the methodology design for this RCT through recommendations from CONSORT (Consolidated Standards of Reporting Trials) Statement.

**Figure 2 F2:**
[figure not shown]
**Research methodology sequence diagram**. The inclusion criteria are as follows: Age ≥ 18 yrs and remain ventilated for ≥ 48 hours; present with documented sepsis or high clinical suspicion of sepsis. Patients with head injuries, burns, spinal injuries, and multiple fractured lower limbs, those with septic shock unresponsive to treatment, moribund or with expected mortality within 48 hours will be excluded.

### Inclusion Criteria

To be eligible for recruitment in the study, participants must be aged 18 years and above; ventilated for ≥ 48 hours; diagnosed with a sepsis syndrome or have a high clinical suspicion of sepsis [57]. Patients with head injuries, burns, spinal injuries, and multiple fractured lower limbs requiring specific rehabilitation regimes and patients with septic shock who are unresponsive to maximal treatment and those who are moribund or have an expected mortality within 48 hours will be excluded.

### Recruitment, Randomisation and Blinding

Eligible patients will be identified and consent will be sought by the chief and principal investigators, with next of kin or substitute decision maker. Participants recruited will be randomized into control and intervention arms using computer generated randomization; http://www.randomization.com/. The randomization sequence will be generated and re-identifiable serial numbers will be assigned by a research personnel not involved in the study. They will be concealed from consent designee research staff for group allocation to prevent selection bias and protected by an electronic password. Participants, substitute decision makers and outcome assessors will be blinded to group allocation to avoid influence over treatment effect. Blinding of the treating physiotherapist and health care providers cannot be ensured due to the nature of the research intervention.

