### Control Arm

Participants allocated to the control arm will receive standard ICU care. The participants randomised to this group will not receive active rehabilitation from the research team, i.e. will not be given targeted exercises early in their disease process upon recruitment. However, they will continue to receive simple and less regular mobilisation activities from other sources, as part of the usual ICU care such as sitting out of bed or ambulation immediately prior to discharge from the unit. The time involved in these activities and the type of activities performed will be recorded and compared between groups.

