### Primary Outcome Measures

All primary outcomes will be measured at baseline (recruitment) and at ICU discharge and quality of life at 6 months post hospital discharge. The primary outcome measures will report the level of physical functioning and quality of life (long-term effects) of the participants. Physical function will be measured using the Acute Care Index of Function (ACIF) and the Physical Function ICU Test (PFIT).

The ACIF will essentially rate simple physical function (transfer bed to chair, sit to stand independently) of the patient on leaving the ICU [62]. The PFIT is a newly developed clinical tool for testing functional strength and endurance capacity in ICU patients. It consists of a battery of tests assessing endurance, muscle strength, cardiovascular capacity and functional ability which are domain representative of physical function and specific for the use of higher functional assessment in the critically ill [63]. These have been chosen as corresponding measuring instruments as they have demonstrated reliability, validity and responsiveness in the ICU population [63,64].

Quality of life will be measured using the Short Form-36 (SF-36) Health Survey Questionnaire. Information from the next of kin will be used to provide proxy scores which have been demonstrated to have good reliability and validity [65].

The constructs of psychological well being will be measured using the anxiety subscale of the Hospital Anxiety and Depression Scale (HADS) as psychological wellbeing is known to be highly correlated to functional physical outcomes [66].

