#### Inflammatory Biomarkers

Biomarkers will be measured before intervention and 30 minutes post intervention daily (week 1) and thereafter twice weekly (till ICU discharge). The acute inflammatory response of early exercise in sepsis will be measured by changes in levels of pro-inflammatory cytokines (IL-6 and TNF-α) and anti-inflammatory cytokine (IL-10). IL-6, IL-10 and TNF-α will be measured from plasma samples with the Milliplex cytokine panels from Millipore (Billerica, MA, USA) using a Luminex 100 assay, with inter and intra-assay CV < 7%.

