#### Muscle oxygenation and Microcirculation

Muscle oxygenation and microcirculatory changes will be measured using the Near Infrared Oxygenation (NIR0) Monitor and the Orthogonal Polarization Spectral (OPS) Microscan respectively.

Muscle (tissue) oxygenation will be measured pre and post intervention daily using the NIRO (NIRO-200, Hamamatsu, Japan) with a probe placed on a peripheral muscle to detect levels of muscle oxygenation (StO_2_) following acute exercise [72]. Muscle oxygen consumption will be further analysed through induced ischemia and active hyperaemia [73]. A pneumatic cuff will be placed above the elbow and inflated to 50 mmHg above the patient's systolic blood pressure and the occlusion will be retained for 3 minutes inducing local ischemia. StO_2 _will be recorded continuously for 3 minutes before, during and after arterial occlusion [44].

Improvements in microcirculation following acute exercise will be measured pre and post intervention session once weekly using the OPS MicroScan (Microvision Medical Inc, Wallingford, PA, USA) with a non-invasive probe placed in the sub-lingual space to detect functional capillary density and blood flow velocity as indicators of microcirculatory function [74] using video images. Five video sequences per patient will be graded by 3 independent observers and assigned a flow velocity score to each of the 4 quadrants of each image [75]. Capillary density will be calculated using superimposed calibrated grid of vertical and horizontal lines on the images of number of small (< 20 μm) vessels crossing the lines of the grid divided by the total length of the lines, yielding the number of small vessels per millimetre [76]. An average of these 5 readings will be calculated for discrete capillary density value for each time point at which imaging was performed.

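### Participant blinding is claimed but not credible when only one arm does an active exercise programme, and four secondary measures are timed to a session that controls do not have

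*Protocol article*

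**What the plan says.** **Blinding.** Methods and Design opens with "The i-PERFORM Trial is a prospective double blinded randomised controlled trial (RCT) in patients with sepsis syndromes" and adds "All outcomes will be measured by a blinded assessor from the research team". Recruitment, Randomisation and Blinding goes further: "Participants, substitute decision makers and outcome assessors will be blinded to group allocation to avoid influence over treatment effect". It then concedes that the treating physiotherapist and care staff may know the arm, because of what the intervention is.

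**What each arm receives.** Under Intervention Arm, Table 2 ties activity to the Ramsay score. Stage 2 (Ramsay 3-2) already includes active, lightly resisted movement. Ergometry appears in Stages 3 and 4, tilt table in Stage 3 and assisted walking in Stage 4, all at Ramsay 2. Under Control Arm, patients "will not receive active rehabilitation from the research team". They do get some usual-care mobilisation, and its type and duration are recorded and compared. No sham or attention control is described.

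**Who reports the outcomes.** Primary Outcome Measures lists ACIF, PFIT, SF-36 and the HADS anxiety subscale. In the SF-36 paragraph it says: "Information from the next of kin will be used to provide proxy scores".

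**Timing of secondary measures.** For cytokines: "Biomarkers will be measured before intervention and 30 minutes post intervention daily (week 1", then twice weekly. Lactate has the same before-and-30-minutes-after anchor. "Muscle (tissue) oxygenation will be measured pre and post intervention daily", and microcirculation is read before and after a session once a week.

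**The concern.** There are two separate problems.

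First, the article asserts a property that the design cannot deliver. The reason it gives for not blinding the physiotherapist, namely the nature of the intervention, applies equally to the awake patient who performs the exercise. If the label stands, the SF-36 and HADS results will be read as blinded when they are in effect open-label. Quality of life is part of the primary hypothesis, so this is not a side issue.

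Second, a pre/post change around an exercise session needs a control interval. Without one, the change in the intervention arm mixes the effect of the session with time of day and natural recovery. It then says little about the mechanism that the secondary hypotheses are meant to test.

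**Working it through.** The point contains no figure to recompute, so the check sets the sections side by side.

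**Step 1: can the stated parties be blind?**

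- *Participants.* Table 2 has awake, cooperating patients doing ergometry and assisted walking up to twice daily. The control arm has no study session and no described sham. A patient in the later stages can recognise the programme. The claim fails on the article's own content.
- *Kin.* Consent is sought from the next of kin or substitute decision maker, so those who consent for the patient and those who give proxy scores may be the same people. The programme runs daily until ICU discharge. That visitors can recognise it is an inference, so the claim is doubtful rather than refuted.
- *Assessors.* ACIF and PFIT are taken at recruitment and ICU discharge, away from sessions. A separate assessor can be blind.

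**Step 2: which measures have a time point in both arms?**

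| Measure | Time anchor in the article | Defined for controls as written? |
|---|---|---|
| ACIF, PFIT | recruitment, ICU discharge | yes |
| SF-36, HADS anxiety | recruitment, ICU discharge; quality of life also 6 months after hospital discharge | yes |
| Fat free mass | baseline, weekly | yes |
| mtDNA (own subsection) | baseline, weekly | yes |
| IL-6, IL-10, TNF-α | before and 30 minutes after the session | no |
| Lactate | before and 30 minutes after the session | no |
| StO2 | before and after the session, daily | no |
| Microcirculation | before and after the session, weekly | no |

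The 30-minute interval and the word session rule out reading the anchor as the whole treatment period. Key Messages also places the assessments around exercise sessions. Four of the six secondary measure groups are therefore tied to an event in one arm only. One further sentence, in the opening of Secondary Outcome Measures, lists mtDNA among the pre/post samples. The weekly schedule in its own subsection is not affected.

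**Step 3: does the plan need the control time point?** Data Management and Statistical Analysis plans a repeated-measures ANOVA with effects of time and group. Sample size gives per-group numbers for tissue oxygenation (91) and microcirculation (59), so these are meant as two-group comparisons. In symbols:

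- intervention change = session effect + drift over the interval
- control change = drift over the interval
- difference = session effect, but only if the control interval matches in clock time and study day

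As written, the second line has no defined interval, so the difference is not defined.

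**Step 4: does the correction move any sample size figure?** No. Rewording the blinding claim and adding a control sampling time leave every stated number as it is.

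**The case against.** The strongest reply is that this is a journal article. The full protocol and the flow diagram are not shown, and a time-matched rest period for controls may well exist. That stands as a limit: silence on the control schedule does not show that controls are unsampled or sampled at other times. It does not remove the point, because the article does fix a schedule and fixes it to an event in one arm only. If a matched period exists, one sentence resolves it. The blinding claim is different, since it is a positive statement that the article's own intervention contradicts.

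Several stronger readings are tempting, and the document does not support them.

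- *All blinding fails.* Blind assessment of ACIF and PFIT remains feasible. Knowing the arm when blood is drawn does not unblind a plasma assay or a bench analyser. The microcirculation videos are graded by three independent observers. Bedside StO2 is the main exception, and it is an instrument reading.
- *No between-arm analysis is possible.* The ANOVA can be run for fat free mass and mtDNA. Pre-session samples could also be compared by study day if controls are sampled on a known schedule.
- *Controls are never mobilised.* They are, less often. Seeing a patient sit out or walk does not by itself reveal the arm.
- *Kin also answer the HADS.* Proxies are mentioned only for the SF-36.
- *SF-36 must leave the primary hypothesis.* That is a preference. Patient-reported outcomes can be kept in rehabilitation trials that cannot be blinded, provided the risk is acknowledged.

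**Conclusion.** The point holds on both counts, within the limits above.

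Participant blinding is not credible and kin blinding is doubtful. This concerns the SF-36 (self or proxy) and the HADS anxiety subscale, two of the four instruments under Primary Outcome Measures. The between-arm pre/post contrast has no defined control time point for cytokines, lactate, StO2 and microcirculation.

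The direction and size of any bias cannot be derived from the document. The conclusion rests on two assumptions: that no sham or attention session exists beyond what the article describes, and that the session-timed measures are meant to be compared between arms, as the secondary hypotheses and the analysis section indicate. The second count falls away if the full protocol gives controls matched sampling times. The first does not.

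**What to change.** 1. Replace the double-blinded label with assessor-blinded, and name the outcomes it covers. Withdraw the claim that participants and kin are blinded.
2. Report SF-36, proxy SF-36 and HADS as unblinded and acknowledge the risk of bias. They need not leave the primary hypothesis.
3. For cytokines, lactate, StO2 and microcirculation, choose one of two options and state it:
   - sample controls at clock times and study days matched to the intervention arm; or
   - base the between-arm test on a resting, pre-session sample at a fixed time in both arms, and label the post-session change as descriptive within the intervention arm.
4. Have StO2 read and videos graded without knowledge of the arm where possible. Otherwise state that these readings are not blinded.

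The cost is mainly wording and a fixed sampling schedule. The matched option also requires paired control sampling if that is not already planned. The blinding claim becomes weaker, and under the second option the acute-response result is descriptive only.
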